### Intervention

The participants will be randomly assigned either to the acupuncture (Jin’s Three-Needle) group or the sham acupuncture group. All acupuncture sessions will be performed by acupuncturists from China who are licensed as acupuncturists with more than 3 years of experience in clinics.

Before initiation of the study, the acupuncturists will participate in training sessions to ensure that the skills of the acupuncturists are consistent and receive a brochure that shows the acupuncture manipulation with detailed information. Patients in both groups will undergo 24 acupuncture sessions over the course of 8 weeks (three treatment per week, 30 min per session). Our study will utilize a disposable sterile needle (Hwato, Suzhou, China; lengths and diameters 0.3 mm × 25 mm or 0.3 mm × 40 mm). For the location of acupuncture points, we will refer to the WHO Standard Acupuncture Point Locations in the Western Pacific Region [24]. The schedule of the trial is described in detail in Fig 2.

**Fig 2 pone.0338341.g002:**
[figure not shown]
Schedule of enrolment, interventions, and assessments. Notes: HAMD-17: The 17-item Hamilton Depression Rating Scale; SDS: Self-rating depression scale; PSQI, Pittsburgh sleep quality index; TCMSS: The traditional Chinese medicine syndrome score scale; HAMA: Hamilton Anxiety Scale; SAS: Self-Rating Anxiety Scale.

#### Acupuncture (Jin’s Three-Needle) group.

According to the traditional theory of Jin’s Three-Needle and our previous studies [12,25], acupuncture interventions were developed by a consensus of acupuncture experts. The acupoints selected were “Yusan-zhen, “Dingshen-zhen”, and “Zusan-zhen”, which are commonly used to treat psychiatric disorders. Baihui (GV20), Sishen-I(GV21), Sishen-II(GV19), Sishen-III, Sishen-IV, Dingshen-I, Dingshen-II, Dingshen-III, Neiguan(PC6), Zusanli(ST36), Sanyinjiao(SP6), and Taichong(LR3) acupoints will be used in the acupuncture treatment. PC6, ST36, SP6 and LR3 will be needled at an angle of 45–90° to the participant’s skin, while Dingshen-zhen and Sishen-zhen will be needled at an angle of 15–30° to the skin. The needles will be inserted at a depth of 5–30 mm and the needles will be stimulated by manual rotation to achieve the typical acupuncture sensation of de qi, which is characterized as soreness, numbness and heaviness. Needles will be retained for 30 min and manually stimulated every 10 minutes. The location of acupuncture points is described in Table 1 and Fig 3.

**Table 1 pone.0338341.t001:** Framework of the acupuncture point prescription.

Acupuncture points	Description
** *Sishen-I(GV21)* **	On the head, 3.5 B-cun superior to the anterior hairline, on the anterior median line.
***Sishen-II* (GV19)**	On the head, 5.5 B-cun superior to the posterior hairline, on the posterior median line.
**GV20: Baihui**	On the head, 5B-cun superior to the anterior hairline, on the anterior median line.
** *Sishen-III* **	On the head, 1.5*cun* left lateral to the anterior median line and at the same level as GV20.
** *Sishen-IV* **	On the head, 1.5*cun* right lateral to the anterior median line and at the same level as GV20
**EX-HN3: Yintang**	On the head, between the right medial end of the eyebrow and the left one.
** *Dingshen-I* **	On the head, directly 0.5*cun* superior to EX-HN3
**GB14: Yangbai**	On the head, 1B-cun superior to the eyebrow, directly superior to the centre of the pupil.
** *Dingshen-II* **	On the head, directly 0.5*cun* superior to left GB14
** *Dingshen-III* **	On the head, directly 0.5*cun* superior to right GB14
**PC6: Neiguan**	On the anterior aspect of the forearm, between the tendons of the palmaris longus and the flexor carpi radialis, 2B-cun proximal to the palmar wrist crease.
**ST36: Zusanli**	On the anterior aspect of the leg, on the line connecting ST35 with ST41, 3 B-cun inferior to ST35.
**SP6: Sanyinjiao**	On the tibial aspect of the leg, posterior to the medial border of the tibia, 3 B-cun superior to the prominence of the medial malleolus.
**LR3: Taichong**	On the dorsum of the foot, between the first and second metatarsal bones, in the depression distal to the junction of the bases of the two bones, over the dorsalis pedis artery.

The prescribed of acupoints are come from the WHO Standard Acupuncture Point Locations in the Western Pacific Region

**Fig 3 pone.0338341.g003:**
[figure not shown]
Acupuncture points used in the study.

#### Sham acupuncture group.

The sham acupuncture consisted of sham acupoint, shallow needle insertion using thin and short needles at non acupuncture points [26]. Sham acupoints are systematically located near to the verum acupuncture sites. We identified non – meridian regions that are far from the verum acupoints and have no meridian associations as the new sham acupoint locations. (See S3 in the Supplementary file in S1 File). The needle insertion will be gentle, superficial and oblique <5mm, with 30-minute retention time. No needle manipulation will be performed throughout the intervention session. After the trial, all participants in sham acupuncture group will receive vouchers for 24 true acupuncture bonus sessions as compensation.

### Outcomes

#### Primary outcome.

The primary outcome is the change in the 17-item Hamilton Depression Rating Scale (HAMD-17) score from baseline to the end of the 8-week treatment period (Week 8). The HAMD-17 is the most employed classical clinical depression symptom rating scale, which measures five domains related to depression, including anxiety/somatization, weight, cognitive disturbance, psychomotor retardation and sleep disturbance [27]. HAMD-17 consists of 17 items that include 3 (scored from 0 to 2) and 5 (scored from 0 to 4) response variants, which reflect ascending symptom severity levels. Total scores are categorized as follows: 0–7 (normal), 8–24 (mild to moderate depressive disorder), and ≥25 (major depressive disorder).

#### Secondary outcomes.

Secondary outcomes included scores on the Traditional Chinese Medicine Syndrome Score Scale (TCMSS), Pittsburgh Sleep Quality Index (PSQI), Self-rating depression scale (SDS); Hamilton Anxiety Scale (HAMA); Self-Rating Anxiety Scale (SAS).

(1) TCMSS: It consists of 23 items with 3 (scored 0–2), 4 (scored 0–3) and 4(scored 0, 2, 4 and 6) response variants that are scored according to increasing symptom intensity [28]. Higher scores are indicative of “Liver Qi Stagnation” and “Spleen Deficiency” patterns in traditional Chinese medicine, which reflect symptoms of depression. The TCMSS is interpreted as follows: < 40(mild/moderate depressive disorder) and ≥ 40(major depressive disorder).(2) PSQI: It assesses sleep disturbances through seven domains: subjective sleep quality, sleep duration, sleep latency, habitual sleep efficiency, sleep disturbances, daytime dysfunction, and use of sleep medications [29]. Each component is rated on a 4-point Likert-type scale (0–3), with total scores ranging from 0 to 21. Higher scores reflect greater severity of sleep impairment, with a threshold score >5 indicating clinically significant sleep dysfunction.(3) SDS: It developed by [name]K. Zung in 1965, is a psychometric instrument comprising 20 items designed to assess subjective depressive experiences [30]. It employs a 4-point Likert-type scoring system, wherein participants rate item applicability based on symptom occurrence frequency: 1 = Never or rarely; 2 = Occasionally; 3 = Frequently; 4 = Consistently. Higher total scores indicate greater symptom severity, with clinical stratification as follows: 53–62: Mild depression (clinically significant); 63–72: Moderate depression; ≥ 73: Severe depression.(4) HAMA: It developed by Max Hamilton in 1959, is a clinician-administered psychometric instrument originally designed for psychiatric practice [31]. HAMA consists of 14 items, with all items scored on a 0–4 scale using a 5-point rating system. The criteria for each level are as follows: 0 points indicate no symptoms; 1 point indicates mild symptoms; 2 points indicate moderate symptoms; 3 points indicate severe symptoms; and 4 points indicate extremely severe symptoms. The higher the total score, the more severe the anxiety symptoms. Specifically, a total score of ≥29 points may indicate severe anxiety; ≥ 21 points indicate definite significant anxiety; ≥ 14 points indicate definite anxiety; a score above 7 may suggest anxiety; and a score below 7 indicates no anxiety symptoms.(5) SAS: It developed by [name]K. Zung in 1971, is a psychometric instrument comprising 20 items designed to assess subjective anxiety [32]. It employs a 4-point Likert-type scoring system, wherein participants rate item applicability based on symptom occurrence frequency: 1 = Never or rarely; 2 = Occasionally; 3 = Frequently; 4 = Consistently. Higher SAS scores generally reflected more serious levels of anxiety concerns. The cutoff point of SAS score 50 considered as the presence of clinical anxiety concern in Chinese population, with severity stratification as follows: 50–59: Mild anxiety; 60–69: Moderate anxiety; ≥ 70: Severe anxiety.

#### Safety.

In the event of adverse events (AEs), corrective measures and prognostic interventions will be implemented commensurate with the severity of the event. All AEs must be documented, addressed within 24 hours, and subjected to objective, evidence-based evaluation utilizing adverse reaction data. Concurrently, a structured investigation will be conducted to determine whether the AEs are treatment-related, evaluate the therapeutic interventions associated with the events, and assess the potential benefits of modifying the treatment protocol within the trial framework. For minor acupuncture-related AEs (e.g., dizziness, needle stagnation, nausea, hematoma formation, localized infection), participants may continue participation in the early-phase intervention trial only following reconfirmation of informed consent and rigorous exclusion of confounding factors. Participants experiencing severe AEs deemed causally linked to the trial intervention will be immediately withdrawn from the study and provided with appropriate medical treatment in accordance with ethical and clinical guidelines. All acupuncturists and research assessors will be trained in recognizing signs of clinical deterioration and are aware of the emergency referral procedures. Participants who experience significant worsening of their depression will be offered, in consultation with their treating physician, the option to initiate standard antidepressant medication. This would be considered a major protocol deviation and lead to study withdrawal, but their data would continue to be followed for safety analyses.

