**Methods:**

This is a prospective, parallel-arm, single-blind, randomized controlled trial. We plan to enroll 106 participants with mild-to-moderate depression, randomly assigning them to receive either JTN or sham acupuncture (SA) in a 1:1 ratio. All participants will receive the JTN treatment or SA treatment for 8 weeks (3 per week). The primary outcome will be assessed using the 17-item Hamilton Depression Rating Scale (HAMD-17). Secondary outcomes will include the Self-Rating Depression Scale (SDS), Pittsburgh Sleep Quality Index (PSQI), Hamilton Anxiety Scale (HAMA), Self-Rating Anxiety Scale (SAS), and the Traditional Chinese Medicine Syndrome Score Scale (TCMSS). Evaluations will be performed at baseline and at weeks 4, 6, and 8 after treatment initiation. Statistical analyses will be conducted on both the intention-to-treat (ITT) and per-protocol (PP) datasets.

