**Fig 1 pone.0338341.g001:**
[figure not shown]
Flowchart of trial procedures. Notes: HAMD-17: The 17-item Hamilton Depression Rating Scale; SDS: Self-rating depression scale; PSQI, Pittsburgh sleep quality index; TCMSS: The traditional Chinese medicine syndrome score scale; HAMA: Hamilton Anxiety Scale; SAS: Self-Rating Anxiety Scale.

The trial will be conducted in accordance with the Declaration of Helsinki and has been approved by the Ethics Committee of Guangzhou Huangpu District Hospital of Traditional Chinese Medicine (TCMHHP2024120401) and registered with the International Traditional Medicine Clinical Trial Registry (ITMCTR2024000872). This trial is currently recruiting patients, which started on 01 January 2025 and is anticipated to end on 12 December 2026.

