### Sample size calculation

The sample size was determined by utilizing the HAMD-17 scale score as the evaluative index. Based on previous study [33], after 8 weeks of treatment, the HAMD-17 score difference between the baseline and the endpoint in the acupuncture group should be approximately 10.79 ± 1.40, while the sham acupuncture group should be approximately 9.82 ± 1.80. Type 1 error is assumed at 0.05, and type 2 error is assumed at 0.2. PASS11.0 software (NCSS Statistical Software, Kaysville, UT, USA) has been used to determine the sample size, and the minimum sample size is 45 subjects for each group. Considering a dropout rate of 15%, a total of 106 subjects will be required with 1:1 allocation to each group (53 participants per group) for this study.

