### Statistical analysis

Intention-to-treat (ITT) will be used for the complete follow-up analysis. All randomized participants who received at least one treatment session and for whom at least one post-baseline assessment will be included for the full analysis in the full analytic dataset (FAS). Missing data will be replaced according to the principle of multiple imputations. Participants demonstrating strict protocol adherence and completing the full treatment course will be included in the Per Protocol Set (PPS) for efficacy analysis. All randomized participants who received at least one treatment will be included in the Safety Analysis Set (SS).

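### Starting an antidepressant for worsening ends participation with only safety follow-up named, so later HAMD-17 scores appear to be lost and early rescues fall outside the analysis labelled ITT

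*Protocol article*

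**What the plan says.** The rescue rule is in the Safety subsection of Outcomes: "Participants who experience significant worsening of their depression will be offered, in consultation with their treating physician, the option to initiate standard antidepressant medication". The consequence follows in the next sentence: "This would be considered a major protocol deviation and lead to study withdrawal, but their data would continue to be followed for safety analyses".

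The primary outcome is the change in HAMD-17 from baseline to week 8. The abstract fixes the assessment times: "Evaluations will be performed at baseline and at weeks 4, 6, and 8 after treatment initiation".

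Statistical analysis opens with "Intention-to-treat (ITT) will be used for the complete follow-up analysis" and then defines the full analysis set (FAS): "All randomized participants who received at least one treatment session and for whom at least one post-baseline assessment will be included". Missing data are to be multiply imputed. Efficacy is evaluated on the FAS and the per-protocol set, and no wider efficacy set is named.

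**The concern.** The trigger for withdrawal is deterioration in the construct that the primary outcome measures. If HAMD-17 assessment stops at that point, the missing week-8 scores are missing because of the outcome, and they come mainly from participants doing badly.

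Two losses follow:

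- **Rescue after the week-4 assessment.** The participant stays in the FAS, but the week-8 value is imputed. An imputation model informed mostly by participants who were not rescued may give values that are too favourable.
- **Rescue before week 4.** The participant has no scheduled post-baseline assessment, so does not enter the FAS, and cannot enter the per-protocol set, which requires the full treatment course. Imputation does not help someone outside the set being imputed.

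If rescue rates differ between arms, the week-8 comparison is biased. More rescue under JTN flatters JTN; more rescue under sham hides part of its benefit. An analysis plan can decide how to model or score rescue, but it cannot supply assessments that were never made. That is why the point belongs to the protocol.

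**Working it through.** **Inputs from the protocol article.** Under Sample size calculation, the expected HAMD-17 improvement in the acupuncture group "should be approximately 10.79 ± 1.40, while the sham acupuncture group should be approximately 9.82 ± 1.80". The planned difference is 10.79 − 9.82 = 0.97. There are 53 participants per arm, allowing for 15% dropout.

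**The plan's own figure.** With a pooled SD of √((1.40² + 1.80²)/2) = 1.612, two-sided α = 0.05 and power 0.80, the normal approximation gives 44 per group. The t-based calculation needs 45 (power 0.805 at 45, 0.796 at 44). Then 45/0.85 = 52.9, rounded up to 53 per group, 106 in all. The stated size reproduces and is not in dispute.

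**Assumptions.** The documents give no rescue rate. Let kJ and kS be the numbers rescued under JTN and sham, and d their improvement by week 8. Everyone else is at the planned means.

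**Case 1: all rescue before week 4, so the FAS reports 0.97.**

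All-randomised difference = [(53 − kJ)·10.79 + kJ·d]/53 − [(53 − kS)·9.82 + kS·d]/53

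Bias = 0.97 minus that = [kJ·(10.79 − d) − kS·(9.82 − d)]/53

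For example, kJ = 4, kS = 2, d = 0: (43.16 − 19.64)/53 = 0.444.

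| kJ vs kS | d | All-randomised difference | Bias |
|---|---|---|---|
| 4 vs 2 | 5 | 0.715 | +0.255 |
| 4 vs 2 | 0 | 0.526 | +0.444 |
| 4 vs 2 | −3 | 0.413 | +0.557 |
| 2 vs 4 | 5 | 1.115 | −0.145 |
| 2 vs 4 | 0 | 1.304 | −0.334 |
| 2 vs 4 | −3 | 1.417 | −0.447 |
| 2 vs 2 | any | 0.933 | +0.037 |

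For scale, the standard error of the difference at 53 per arm is √((1.40² + 1.80²)/53) = 0.31.

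**Case 2: all rescue after week 6, week 8 imputed from week 6.** Assume equal means and SDs at the two visits, correlation r, and a week-6 score as poor as week 8 would be. The imputed value is m + r·(d − m), where m is the arm mean, so the bias is (1 − r) times that of Case 1. The largest entry (4 vs 2, d = −3) becomes 0.3 × 0.557 = 0.167 at r = 0.7 and 0.1 × 0.557 = 0.056 at r = 0.9.

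**Chance imbalance.** With two independent Binomial(53, 3/53) counts, a gap of two or more arises with probability 0.519; at 1 in 53 it is 0.258. At equal rates this is random error. Systematic bias needs unequal rates.

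**How extreme the assumed outcomes are.** An improvement of 0 lies 10.79/1.40 = 7.7 SD below the planned JTN mean and 9.82/1.80 = 5.5 SD below the sham mean. An improvement of 5 lies 4.1 and 2.7 SD below. The planned SDs leave almost no room for participants who worsen, although the Safety text provides for them.

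**The case against.** The strongest reply is that the premise is inferred. The sentence stands in a safety subsection of a condensed article, where safety use is the natural thing to mention. It does not say that HAMD-17 visits stop, and the assessment schedule (Fig 2) is not reproduced in the text available. The FAS needs a post-baseline assessment, not specifically the week-4 one, so a rating made when worsening is recognised could keep an early rescue in the set. This stands as a caveat: the text neither describes nor excludes such a rating. But a rule that specifies withdrawal and names a single surviving purpose should not leave the reader guessing about the primary endpoint.

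The second reply concerns size. The larger biases need rescue before week 4, a 2:1 imbalance and little or no improvement. Early-rescued participants would have had more than four weeks on an antidepressant by week 8, so d = 5 may be nearer the truth: +0.26 or −0.15. Exclusion of suicidal and treatment-resistant patients, and a planned 9.82-point improvement even under sham, suggest rescue may be rare. All of this is fair, and it limits the severity.

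Third, calling the gap bias presupposes that scores after rescue count as observed, an estimand choice the article does not state. That also stands, and the choice can be left to the analysis plan. Whatever is chosen, collecting the scores keeps the options open, while not collecting them removes this one.

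**Conclusion.** The concern holds, with medium confidence, as something that should be fixed. Followed as written, the rescue rule appears to lose week-8 HAMD-17 scores for outcome-related reasons. Unless a rating is taken at withdrawal, it also removes participants rescued before week 4 from the analysis labelled ITT.

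The effect could range from negligible to more than half of the planned 0.97-point difference, in either direction in principle. It is small if rescue is rare, balanced between arms, or late with informative week-4 and week-6 scores. It becomes material if a few early rescues fall unevenly between arms. The figures are illustrations under assumed rescue counts and outcomes. Equal rates cannot be taken for granted, because the acupuncturists know the allocation and are among those trained to recognise deterioration.

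**What to change.** Leave patient care unchanged and make these changes:

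1. **Safety.** State that starting an antidepressant ends study treatment but not assessment, and that blinded HAMD-17 continues at the remaining scheduled visits through week 8 in consenting participants. If continued assessment or a withdrawal rating is already intended, say so here.
2. **Statistical analysis.** Keep all randomised participants, including those rescued before week 4, in the ITT set.
3. **Analysis plan.** State how scores after rescue are used, since they include any antidepressant effect.

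The cost is at most three already-scheduled visits (weeks 4, 6 and 8) per rescued participant, plus a protocol amendment. The sample size stays at 106. The article reports: "This trial is currently recruiting patients, which started on 01 January 2025". Scores already missed cannot be recovered, so the amendment should be made promptly.

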### Quality control, data management and monitoring

Prior to participant recruitment, all team members will be required to complete a standardized training workshop to ensure strict adherence to the study protocol and comprehensive understanding of trial administration procedures. The interventions will be performed by licensed acupuncturists with more than 3 years of experience in hospital. The acupuncturists will also receive a brochure about the protocol and standard operating procedures of acupuncture (Jin’s Three-Needle).

All data will be systematically collected and recorded in case report forms (CRFs) with chain-of-custody documentation. All data will be entered into a password-protected computer by research personnel unaware of the group assignments. The data will then be double-checked by investigators following data entry. Data quality will be regularly monitored by research assistants and overseen by monitors. The original CRFs and all other forms will be archived securely at the Clinical Research Center of Guangzhou Huangpu District Hospital of Traditional Chinese Medicine.

The Clinical Research Center of Guangzhou Huangpu District Hospital of Traditional Chinese Medicine will be responsible for several key aspects of this trial: monitoring the data, managing regulatory compliance, conducting independent audits every three months without influence from investigators or the sponsor, and determining if any premature closure of the study is necessary.

### Sample size calculation

The sample size was determined by utilizing the HAMD-17 scale score as the evaluative index. Based on previous study [33], after 8 weeks of treatment, the HAMD-17 score difference between the baseline and the endpoint in the acupuncture group should be approximately 10.79 ± 1.40, while the sham acupuncture group should be approximately 9.82 ± 1.80. Type 1 error is assumed at 0.05, and type 2 error is assumed at 0.2. PASS11.0 software (NCSS Statistical Software, Kaysville, UT, USA) has been used to determine the sample size, and the minimum sample size is 45 subjects for each group. Considering a dropout rate of 15%, a total of 106 subjects will be required with 1:1 allocation to each group (53 participants per group) for this study.

